**LIST OF ABBREVIATIONS AND RELEVANT DEFINITIONS**

|                |                                                                                                                                                                                                             |
|----------------|-------------------------------------------------------------------------------------------------------------------------------------------------------------------------------------------------------------|
| ABR     | ABR form, General Assessment and Registration form, is the application form that is required for submission to the accredited Ethics Committee (In Dutch, ABR = Algemene Beoordeling en Registratie) |
| ABPA    | Allergic Bronchopulmonary Aspergillosis                                                                                                                                                              |
| AE      | Adverse Event                                                                                                                                                                                        |
| AR      | Adverse Reaction                                                                                                                                                                                     |
| AUC     | Area Under the Curve                                                                                                                                                                                 |
| Cmax    | Maximum Plasma Concentration                                                                                                                                                                         |
| CA      | Competent Authority                                                                                                                                                                                  |
| 1. CCMO | Central Committee on Research Involving Human Subjects; in Dutch: Centrale Commissie Mensgebonden Onderzoek                                                                                          |
| CF      | Cystic Fibrosis                                                                                                                                                                                      |
| CFU     | Colony Forming Units                                                                                                                                                                                 |
| CHMP    | Committee for Medicinal Products for Human Use                                                                                                                                                       |
| CL      | Clearance                                                                                                                                                                                            |
| CV      | Curriculum Vitae                                                                                                                                                                                     |
| DP      | Dry Powder                                                                                                                                                                                           |
| DPI     | Dry Powder Inhaler                                                                                                                                                                                   |
| DSMB    | Data Safety Monitoring Board                                                                                                                                                                         |
| ERS     | European Respiratory Society                                                                                                                                                                         |
| EU      | European Union                                                                                                                                                                                       |
| EudraCT | European drug regulatory affairs Clinical Trials                                                                                                                                                     |
| F       | Bioavailability                                                                                                                                                                                      |
| FEV1    | Forced Expiratory Volume in one second                                                                                                                                                               |
| GCP     | Good Clinical Practice                                                                                                                                                                               |
| HR-CT   | High Resolution Computed Tomography Scan                                                                                                                                                             |
| IB      | Investigator's Brochure                                                                                                                                                                              |
| IC      | Informed Consent                                                                                                                                                                                     |
| IMP     | Investigational Medicinal Product                                                                                                                                                                    |
| IMPD    | Investigational Medicinal Product Dossier                                                                                                                                                            |
| Ka      | absorption rate constant                                                                                                                                                                             |
| METC    | Medical research ethics committee (MREC); in Dutch: medisch ethische toetsing commissie (METC)                                                                                                       |
| PVC     | Polyvinyl Chloride                                                                                                                                                                                   |
| (S)AE   | (Serious) Adverse Event                                                                                                                                                                              |

|                           |                                                                                                                                                                                                                                                                                                                                                  |
|---------------------------|--------------------------------------------------------------------------------------------------------------------------------------------------------------------------------------------------------------------------------------------------------------------------------------------------------------------------------------------------|
| SPC                | Summary of Product Characteristics (in Dutch: officiële productinformatie IB1-tekst)                                                                                                                                                                                                                                                      |
| Sponsor            | The sponsor is the party that commissions the organisation or performance of the research, for example a pharmaceutical company, academic hospital, scientific organisation or investigator. A party that provides funding for a study but does not commission it is not regarded as the sponsor, but referred to as a subsidising party. |
| SUSAR              | Suspected Unexpected Serious Adverse Reaction                                                                                                                                                                                                                                                                                             |
| T1/2 el | Terminal elimination half-life                                                                                                                                                                                                                                                                                                            |
| Tmax    | Time to maximum plasma concentration                                                                                                                                                                                                                                                                                                      |
| TIP                | Tobramycin Inhalation Powder                                                                                                                                                                                                                                                                                                              |
| TIS                | Tobramycin Inhalation Solution                                                                                                                                                                                                                                                                                                            |
| UMCG               | University Medical Center Groningen                                                                                                                                                                                                                                                                                                       |
| Wbp                | Personal Data Protection Act (in Dutch: Wet Bescherming Persoonsgegevens)                                                                                                                                                                                                                                                                 |
| WMO                | Medical Research Involving Human Subjects Act (in Dutch: Wet Medisch-wetenschappelijk Onderzoek met Mensen)                                                                                                                                                                                                                               |

## SUMMARY

**Rationale:** Bronchiectasis is a persistent and frequently progressive condition characterized by dilated and thick-walled bronchi retaining sputum. There are multiple underlying causes, of which cystic fibrosis (CF) is the best known, but frequently no cause can be identified. The main symptoms of bronchiectasis are cough and chronic sputum production. There is a state of constant colonization with bacteria, which frequently causes exacerbations. The presence of *Pseudomonas aeruginosa* is an unfavorable prognostic indicator and is associated with increased sputum production, more extensive bronchiectasis on HR-CT of the thorax, more hospitalizations and reduced quality of life. Until now, most patients with non-CF bronchiectasis who are colonized with *P. aeruginosa* receive inhaled tobramycin every other month, by use of a nebulizer. However, this delivery system has several disadvantages, like a low lung deposition and pollution with tobramycin in the surrounding environment. With an efficient dry powder inhaler (DPI), a three to six fold higher lung deposition compared to a nebulizer can be obtained. Therapy with a DPI is also less time consuming compared to nebulisation. Nebulised tobramycin is used most in routine care; there is also one, rather poorly characterized DPI for tobramycin available, though this DPI is not registered for non-CF bronchiectasis. We will investigate dry powder tobramycin (DP tobramycin) in a novel device in patients with non-CF bronchiectasis colonized with *P. aeruginosa*.

**Objective:** The main objectives are to investigate the pharmacokinetic properties of DP tobramycin at different dosages together with the local tolerability of DP tobramycin via the Cyclops® at different dosages.

**Study design:** single center, single ascending, single dose, response study.

**Study population:** 8 patients with non-CF bronchiectasis

**Main study parameters/endpoints:**

The following pharmacokinetic parameters will be calculated: actual dose (dose minus remainder in inhaler after inhalation), AUC0-12 (area under the curve from 0 -12 h), Cmax (maximum plasma concentration), Tmax (time to maximum plasma concentration), Ka (absorption rate constant), T1/2 el (terminal elimination half-life), CL/F (clearance following pulmonary administration (F= bioavailability)).

Local tolerability of DP tobramycin is determined by scoring adverse events, specifically coughing, and lung function measurement.

**Nature and extent of the burden and risks associated with participation, benefit and group relatedness:** All participants included in this study are patients recruited from the outpatient department of pulmonology. Before using the DPI they will receive instructions and their inspiratory flow will be tested. Before each test dose an infusion needle will be inserted

and after each test dose blood will be collected. To investigate safety, lung function tests will be performed and the occurrence of adverse events will be scored.

## 2. INTRODUCTION AND RATIONALE

### **Bronchiectasis**

Bronchiectasis is a persistent and frequently progressive condition characterized by dilated and thick-walled bronchi. This pathology can result from many underlying conditions, including post-infectious conditions, like bacterial, mycobacterial (Lady Windermere Syndrome) and viral infections or aspergillus infections. Other causes are of congenital origin, like cystic fibrosis, primary ciliary dyskinesia, alpha-1-antitrypsin deficiency, or Mounier-Kuhns' and Marfan's syndromes; or immuno-deficiencies, both primary like Common Variable Immuno-Deficiency and secondary (e.g., due to hemato-oncological disease). Moreover, toxic inhalation, gastric or foreign body aspiration and rheumatic diseases, like rheumatoid arthritis, systemic lupus erythematosus or Sjögren's syndrome, can be a cause as well. Lastly, there is a large group of other conditions as cause of bronchiectasis. Examples of this group are allergic bronchopulmonary aspergillosis (ABPA), Yellow Nail Syndrome, and inflammatory bowel syndrome 

The main symptoms of bronchiectasis are cough and chronic sputum production. The sputum is described as mucoid, mucopurulent, thick, tenacious or viscous. Blood-streaked sputum or hemoptysis can result from erosive airway damage caused by an acute infection. The presence (colonization) of bacteria such as *P. aeruginosa* and *H. influenzae* can stimulate neutrophilic and inflammatory mediator responses in the airways (Angrill, Agusti et al. 2001). In different studies *H. influenzae* was isolated in 29-42 percent and *P. aeruginosa* was isolated in 13-31 percent of the patients with steady state non-CF bronchiectasis 

### ***Pseudomonas aeruginosa***

*P. aeruginosa* is a gram-negative, motile, non-fermenting, obligate aerobic rod. It is commonly present in soil, water, sewage, plants and animals. Patients colonized with *P. aeruginosa* are a major reservoir and person-to-person contacts serve as an important mode of transmission, especially in hospitals. Respiratory infections due to transmission occur mostly in patients with impaired broncho-pulmonary function, like bronchiectasis, and systemic immune deficiencies.

The presence of *P. aeruginosa* in patients with bronchiectasis is associated with increased sputum production, more extensive bronchiectasis on HR-CT of the thorax, more hospitalizations and reduced quality of life 

### **Inhalation therapy in bronchiectasis**

Nowadays treatment for patients having non-CF bronchiectasis who are colonized with *P. aeruginosa* consists of inhalation therapy with tobramycin or colistin in combination with oral macrolides. Tobramycin is in most cases administered by use of a nebulizer, for 28 days in 2 doses of 300 mg each. Thereafter, 28 days without therapy (or with colistin) follow, after which the cycles repeat. Occasionally, other pathogens like *Enterobacter* spp or mixed infections with similar clinical challenges and difficulties are encountered requiring a similar therapeutic approach. An alternative novel, commercial dry powder tobramycin device exists but has not been well characterized nor had it achieved broad market acceptance. No studies have been done in non CF-bronchiectasis, vide infra.

### **Tobramycin inhalation by wet nebulization**

The currently broadly applied nebulisation technique for administration of antibiotics to patients with infectious lung diseases is ineffective, time consuming and therefore, burdensome to the patient. Furthermore, nebulisation brings the risk of auto-re-infection of the patient (contamination of nebulisation fluid and/or device). Another drawback is the low lung deposition, with several studies showing a mere 10% lung deposition of tobramycin using a nebulizer-compressor (de Boer, Hagedoorn et al. 2006). Nebulizers require space and time: carrying on during travel is problematic, and much time is required for nebulization, which is burdening and jeopardizing adherence with therapy. Dry powder inhalation of antibiotics with a more effective lung deposition can be an interesting alternative, as it can be simple, easy to carry-on, cheap and therefore disposable. This eliminates the need for regular disinfection while a cold chain for storage and the reconstitution of the drug is not needed .

### **Tobramycin inhalation by dry powder**

Dry powder inhalation of tobramycin in higher dosages was first described by Geller et al. They studied tobramycin inhalation powder (TIP, delivered via the Podhaler device) in patients with CF, colonized with *P. aeruginosa*. Both safety and efficacy of a dose of 112 mg TIP compared to a dose of 300 mg nebulized tobramycin solution were studied with comparable pharmacokinetic parameters for both forms of inhalation . A recent study, the EVOLVE trial, compared TIP to placebo in patients with CF colonized with *P. aeruginosa*. TIP reduced sputum *P. aeruginosa* density, respiratory related hospitalization and antipseudomonal antibiotic use . Another study, the EAGER trial, compared 112 mg TIP to 300 mg nebulized tobramycin inhalation solution (TIS). Increases in FEV1% predicted from baseline to day 28 of cycle 3 were similar between groups. The mean reduction in sputum *P. aeruginosa* density (log10 CFU/g) on day 28 of cycle 3 was also comparable between groups. As expected, administration time was significantly less for TIP. Treatment

satisfaction was significantly higher for TIP on a scale of effectiveness, convenience, and global satisfaction. The rate of cough suspected to be study drug related was higher in TIP-treated patients (TIP: 25.3%; TIS: 4.3%) . A disadvantage is the hygroscopicity of the TIP formulation. This makes TIP preservable for a maximum of 7 days. TIP is manufactured by Novartis and, is registered as TOBI® Podhaler®, and has been approved in the European Union by the Committee for Medicinal Products for Human Use (CHMP) in September 2010 for cystic fibrosis. It is now marketed and reimbursed in the Netherlands.

### Novel dry powder inhaler (the Cyclops®)

Good performance of a dry powder inhaler (DPI) depends on the balance achieved between three types of forces, the interparticulate forces in the powder, the de-agglomeration forces during inhalation, and the deposition forces in the human lungs (see fig. 1).

The DPI used in this study was developed at the department of Pharmaceutical Technology and Biopharmacy of the University of Groningen. It was specifically designed to deliver high doses of dry powder drugs, for example antibiotics. Its dispersion principle is based on patented air classifier technology, which enables a reduction of the influence of the patient's breathing behavior on drug delivery (see fig. 2).

Background and justification over dry powder inhalation, especially with aminoglycosides, will be explained further in paragraph 5.6.3

**Figure 1:** Schematic overview of the balance between three types of forces to achieve a good performance of a dry powder inhaler.

[figure not shown]

**Figure 2. the Cyclops®**[figure not shown]

## Tobramycin

The tobramycin formulation used consists of tobramycin free-base, whereas tobramycin sulphate is used in TOBI® nebulizer solution. Switching from one salt to another, or as in this case, to the unassociated form, is allowed when bioavailability, pharmacokinetics and toxicological profile are equivalent. Both the free base and the sulphate are freely soluble in water. Therefore, we believe the free base will behave similarly when it enters the airways. Upon dissolution in the humid environment of the airways, tobramycin sulphate dissociates immediately, and tobramycin becomes available as free base. Presenting tobramycin free base directly or after immediate dissociation, presumably does not affect its pharmacokinetics. To assess pharmacokinetics and to rule out any chance on giving a dose that might induce unacceptable side effects, a safety and dose escalation regime is chosen for the pilot study, with sufficient time for complete washout prior to the administration of the next dose.

## Current protocol

This study will investigate both the pharmacokinetic parameters and the local tolerability inhalation of dry powder tobramycin using the Cyclops® in patients with non-CF bronchiectasis with four different dosages. The first dose of 30 mg is chosen because this dose has the best dispersing properties with in vitro experiments. This last dose (240 mg) is generally considered safe, and it is still lower than the dose normally given as first dose intravenously in patients with sepsis of unknown origin.

Tobramycin by nebulization for non-CF bronchiectasis is routinely administered at a dose of 300 mg twice a day. Until now, as far as we know, no studies have investigated inhalation of tobramycin by nebulisation or as dry powder in patients with non-CF bronchiectasis colonized with *P. aeruginosa* (the studies with the Novartis compound mentioned earlier were in CF-bronchiectasis, a different disease at generally much younger age). In patients with CF bronchiectasis tobramycin inhalation powder showed similar results with a dose of 112 mg compared to a dose of 300 mg nebulized tobramycin solution.

However, as we are most interested in clinical and microbiological response, an efficacy and safety study will be planned after the current proposal. That study will compare TOBI® inhalation solution (the current routine treatment) and dry powder inhalation of tobramycin via the Cyclops® in different treatment strategies. The treatment regimen of DP tobramycin using the Cyclops® will be chosen based on the PK parameters of this study

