### 6.3 Summary of findings from clinical studies

Several studies in the CF population with inhaled tobramycin were done in the late eighties and early nineties of the last century with promising results. However not all therapies that are effective in CF are effective in non-CF bronchiectasis.

Later, studies with tobramycin solution for inhalation were performed in patients with non-CF bronchiectasis. Barker et al investigated 74 patients divided in 2 groups. 37 patients received 300 mg tobramycin solution via a nebulizer twice daily for 28 days, the others received placebo. The patients treated with tobramycin had a significant reduction in sputum *P. aeruginosa* density at all time points of the study. The placebo group had a negligible change in sputum density at all time points. Unfortunately, the incidence of dyspnoea, chest pain and wheezing was significantly greater in the tobramycin group. Orriols et al studied 17 patients with non-CF bronchiectasis colonised with *P. aeruginosa*, divided in 2 groups. Group A received both tobramycin and ceftazidim via nebulisation inhalation and group B was treated symptomatically. One patient in group A withdrew due

to bronchospasm despite intense bronchodilator treatment. One patient in group B died due to respiratory failure after 300 days of follow up. No differences in lung function or arterial blood gas analysis were seen between the two groups. There was only one hospital admission in group A and 7 patients who had to be admitted in group B. In both groups *P. aeruginosa* was still present. They did not study sputum density .

Couch et al studied 74 patients with non-CF bronchiectasis colonized with *P. aeruginosa*. Patients were evenly divided in two groups, one group is receiving tobramycin inhalation therapy and the other group receives placebo. The treatment group received tobramycin for 4 weeks 300 mg twice daily. This group had a significant reduction in sputum *P. aeruginosa* density while the placebo group showed no change. The incidence of dyspnoea, wheezing and chest tightness was again significantly greater in the tobramycin group .

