#### **7.3.7 Adverse effects**

Spirometry will be used to test for adverse broncoconstrictive reactions due to the inhalation, immediately before, 15, 30 and 90 minutes after inhalation. It will be performed by standardized procedure according to the ERS guidelines and reference values. A 10% or more decrease in FEV1 (in mL) will be considered clinically relevant.

Other adverse effects will be asked by the investigator for spontaneous reporting. Special attention will be for cough and dyspnea.

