### **10.3 Benefits and risks assessment, group relatedness**

No direct benefits to participants are expected. The risks are deemed relatively minor; there could be transient cough or dyspnea reactions immediately following inhalation.

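### Section 2 denies that nebulised tobramycin has been studied in non-CF bronchiectasis although 6.3 and 12.1 describe such studies, and two of the symptom groups they report as increased, wheezing and chest pain or tightness, are not named in the tolerability scoring

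*Protocol*

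**What the plan says.** **On earlier evidence.** Section 2 (Current protocol) says that, to the authors' knowledge, "no studies have investigated inhalation of tobramycin by nebulisation or as dry powder in patients with non-CF bronchiectasis colonized with" *P. aeruginosa*. Section 6.3 says: "Later, studies with tobramycin solution for inhalation were performed in patients with non-CF bronchiectasis". It then describes three reports:

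- A 74-patient report in which "37 patients received 300 mg tobramycin solution via a nebulizer twice daily for 28 days, the others received placebo". On adverse effects: "Unfortunately, the incidence of dyspnoea, chest pain and wheezing was significantly greater in the tobramycin group".
- A 17-patient study of nebulised tobramycin combined with ceftazidime in colonised patients, with one withdrawal for bronchospasm in the treated group.
- A second 74-patient report, in colonised patients, of the same dose for four weeks against placebo: "The incidence of dyspnoea, wheezing and chest tightness was again significantly greater in the tobramycin group".

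Section 12.1 (item b) repeats all three reports, and item e repeats the first.

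**On tolerability.** The Summary determines local tolerability by "scoring adverse events, specifically coughing, and lung function measurement". Section 7.1.1 lists an FEV1 drop of more than 10% and adverse events, without naming symptoms. Section 7.3.7 has the investigator ask about other adverse effects for spontaneous reporting and adds: "Special attention will be for cough and dyspnea". Section 10.3 tells the ethics committee: "The risks are deemed relatively minor; there could be transient cough or dyspnea reactions immediately following inhalation".

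**The concern.** The protocol contradicts itself on whether its target population has been studied with the nebulised form of the drug. That would be a background slip, except that the studies Section 2 overlooks are the protocol's own controlled evidence on respiratory symptoms in this disease.

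Section 3 makes local tolerability in the target population a primary objective. Section 4 sets nebulised tobramycin as the benchmark that local intolerability should not exceed. One would therefore expect the symptoms reported as increased with nebulised tobramycin in this population to be among those asked about by name. Dyspnoea is. Wheezing and chest pain or tightness are not. At stake is how consistently these symptoms are recorded across four doses in eight patients, and whether they can be compared with the benchmark.

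**Working it through.** The protocol gives no rates for these symptoms and no formal sample-size inputs, so no calculation applies. The check sets the passages side by side.

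**Step 1: is the contradiction exact?** Drug, route and population must match.

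- Drug and route: all three reports in 6.3 used nebulised tobramycin, one of them together with ceftazidime.
- Population: the second 74-patient report and the 17-patient study are described as non-CF bronchiectasis colonised with *P. aeruginosa*. That is the population in the Section 2 sentence.
- Dry powder: nothing in 6.3 or 12.1 describes dry powder tobramycin in non-CF bronchiectasis, and another paragraph of Section 2 says the marketed powder has not been studied there.

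The sentence is therefore contradicted for nebulisation and not for dry powder.

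**Step 2: which symptoms were reported as increased, and which are targeted?**

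| Symptom | First 74-patient report | Second 74-patient report | Named in the Summary or 7.3.7 | Objective measure |
|---|---|---|---|---|
| Dyspnoea | increased | increased | yes (7.3.7) | FEV1, in part |
| Wheezing | increased | increased | no | FEV1, as proxy for bronchoconstriction |
| Chest pain | increased | not listed | no | none |
| Chest tightness | not listed | increased | no | none |
| Cough | not listed | not listed | yes (both) | none |

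Not listed means only that the protocol's short summary of the report does not mention the symptom.

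**Step 3: how would the unnamed symptoms be recorded?**

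- Section 12.1 (item c) says patients are questioned for adverse events, and 7.3.7 provides for an enquiry that appears to be open.
- Section 8.2.1 records every event that is volunteered or observed.
- Section 9.1 counts subjects with adverse effects without restricting them to named symptoms.
- Spirometry is done immediately before inhalation and at 15, 30 and 90 minutes after it, expressly to detect bronchoconstriction.

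Wheezing thus has an open enquiry and a proxy measurement. Chest pain or tightness has the open enquiry only. Neither has the prompt by name that cough and dyspnoea receive.

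**Step 4: is the risk described elsewhere?** Section 12.1 states the dyspnoea, wheezing and chest findings in full. Section 6.4.1 names bronchospasm, and 12.1 (item j) foresees treatment of bronchoconstriction. Only the brief text of 10.3 is limited to cough and dyspnoea.

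**The case against.** The strongest reply is that the two halves are not causally linked. The Section 2 sentence is background; no outcome, dose or procedure is derived from it, and correcting it would change no measurement. That stands. The case for naming more symptoms rests on 6.3 and on the primary objective, not on the faulty sentence.

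A second reply is that the chosen emphasis is reasonable. Cough is a formulation-specific concern for a powder: Section 2 cites a CF trial with drug-related cough in 25.3% on powder against 4.3% on nebulised solution, and 6.4.1 lists cough and dyspnoea among common effects of a nebulised product. That stands too, so cough should stay. Its absence from the summaries in 6.3 does not show that cough was not increased in those studies.

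A third reply is that nothing is lost, because patients are asked, all events count and FEV1 is a named criterion. This stands in large part. A reader might infer that wheezing and chest symptoms would go unrecorded, or that a dose could be called tolerable with known effects left out; the documents do not support that. What remains is the difference between an open question and a prompt by name, which the protocol itself thought worth making for cough and dyspnoea.

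Two limits also hold. The earlier reports concern four weeks of twice-daily dosing, whereas this study gives separate single doses, so rates may differ. And the two 74-patient reports share size and regimen, and the reference list shows a shared author. They may be one trial and should not be read as independent replication.

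**Conclusion.** The contradiction is real and does not depend on whether the two 74-patient reports are one trial. The qualification about the authors' knowledge does not cure it, because the same protocol cites the studies. On its own it is a minor correction.

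The part that bears on the study is modest. Of the three symptom groups reported as increased (dyspnoea, wheezing, chest pain or tightness), one is named for attention and two are not; of those two, only wheezing has an objective proxy. No loss of detection can be put in figures: the protocol gives neither symptom rates nor the share of cases an open question would pick up, and any number would rest wholly on assumption.

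A reader might also infer that the protocol's risk assessment as a whole understates these effects. It does not: 12.1 reports them in full, and only 10.3 falls short of 6.3 and 12.1. The conclusion assumes that prompting by name records such symptoms more consistently than an open question. It is a recommendation for an inexpensive improvement.

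**What to change.** - **Section 2, Current protocol:** limit the statement to dry powder tobramycin and refer to 6.3 for the studies with nebulised tobramycin.
- **Summary and 7.3.7:** name wheezing and chest pain or tightness, alongside cough and dyspnoea, as symptoms asked about at every dosing visit.
- **Reporting:** give the proportion of patients with each of these symptoms at each dose, alongside the overall proportion with any adverse effect.
- **Section 10.3:** bring the short risk statement into line with 6.3 and 12.1.

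The withdrawal criteria are not touched by this point and stay as they are.

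The cost is wording in four places and two further questions per dosing visit: 2 questions x 4 visits = 8 per patient who completes all doses. No visit, procedure or patient is added. The downside is that asking by name will record somewhat more mild events, which should be kept in mind when the results are set against studies that did not ask in this way.
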